**Methods and analysis:**

FIRE CORAL is a multicenter prospective cohort study of participants recovering from COVID-19 disease with in-person follow-up for functional and pulmonary phenotyping conducted by the National Heart, Lung and Blood Institute (NHLBI) Prevention and Early Treatment of Acute Lung Injury (PETAL) Network. FIRE CORAL will include a subset of participants enrolled in Biology and Longitudinal Epidemiology of PETAL COVID-19 Observational Study (BLUE CORAL), an NHLBI-funded prospective cohort study describing the clinical characteristics, treatments, biology, and outcomes of hospitalized patients with COVID-19 across the PETAL Network. FIRE CORAL consists of a battery of in-person assessments objectively measuring pulmonary function, abnormalities on lung imaging, physical functional status, and biospecimen analyses. Participants will attend and perform initial in-person testing at 3 to 9 months after hospitalization. The primary objective of the study is to determine the feasibility of longitudinal assessments investigating multiple domains of recovery from COVID-19. Secondarily, we will perform descriptive statistics, including the prevalence and characterization of abnormalities on pulmonary function, chest imaging, and functional status. We will also identify potential clinical and biologic factors that predict recovery or the occurrence of persistent impairment of pulmonary function, chest imaging, and functional status.

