To address this urgent need for studies that advance understanding of the clinical spectrum of PASC, we describe a protocol for a prospective observational study, the Functional, Imaging, and Respiratory Evaluation (FIRE) of hospitalized patients following COVID-19 (FIRE CORAL), to (1) examine the feasibility of longitudinal assessments investigating multiple domains of recovery in parallel and (2) elucidate the recovery from COVID-19 disease following acute hospitalization with an emphasis on functional, imaging, and respiratory evaluation. The study procedures and assessments chosen by our investigative team for this protocol measure impairments and syndromes commonly described by patients during routine clinical care following COVID-19.

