### FIRE CORAL study aim

The objectives of the FIRE CORAL study are:Primary: To examine the feasibility of conducting rigorous in-person follow-up testing of participants discharged from the hospital following COVID-19 illness to assist with planning for a larger study to evaluate variables associated with differential recoverySecondary: To describe the pulmonary, imaging, and functional recovery following COVID-19 hospitalization in a diverse population of patients. FIRE CORAL extends the BLUE CORAL study follow-up to include in-person study visits for pulmonary phenotyping and functional assessment

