### Study procedures

*FIRE CORAL* consists of a battery of in-person assessments objectively measuring pulmonary function, abnormalities on lung imaging, and functional status. Participants will attend and perform initial in-person testing at 3 to 9 months after hospital discharge (Table 1, Fig. 3). Participants with abnormal findings on pulmonary function testing or chest imaging during their initial assessment or those with persistent respiratory symptoms will be eligible to repeat study procedures 3 months later with a subsequent visit at 12 months. All participants will be invited to return for in-person follow-up at 12 months after hospital discharge. Imaging and clinical assessments performed as part of routine clinical care within the specified study timeframe will be used in lieu of dedicated study procedures.

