### Statistical methods

#### Sample size

For this pilot study, the target enrollment was chosen to balance characterizing the range of PASC abnormalities against the time constraints associated with COVID-19 research and the waning pandemic with widespread vaccination. Based on these criteria, the target enrollment of 80 participants was felt to be sufficient to provide an urgently needed, preliminary understanding of longer-term respiratory manifestations after COVID-19 infection sufficient to guide future post-COVID pulmonary studies. Our sample size was purposefully chosen to be small to demonstrate the feasibility of conducting longitudinal in-person research in COVID survivors with an understanding that larger studies would be needed to define disease trajectories and identify clinical predictors with small effects [26]. The sample size of 80 was determined for based on multiple factors including the availability of participants enrolled in BLUE CORAL, the number of participating sites, and previous feasibility studies. Sample sizes for pilot and feasibility studies “should be representative of the target study population,” [27] and in general, there are limited evidence to justify sample size of feasibility studies [26]. Research on feasibility studies recommend sample size estimates based on a confidence interval approach: an expected completion rate of 75% with lower bound of the CI = 70%, a total of 75 participants would be needed [27]. Finally, Sim and Lewis suggest that a sample size of 50 should be utilized for pilot studies of randomized controlled trials (RCT) [28]. Our proposed feasibility study will be deemed successful if at least 50 participants out of proposed 80 (62.5%, 95% CI 52–73%) complete at least one study visit.

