#### Statistical analysis plan

To examine the feasibility of long-term follow-up, we will describe the number of participants enrolled and the proportion that returned for in-person follow-up (primary objective). We will perform summary or descriptive statistics to describe the prevalence of abnormalities of pulmonary function, chest CT imaging, and functional status in the enrolled participants (secondary objective). Among participants who return for a 12-month visit, we will describe the trajectory of recovery of pulmonary function and functional status between first and last study visits. Additionally, we will test the relationships (correlative analyses) between outcomes with key independent variables including participant demographics, severity and duration of illness, pre-hospital function, and exposure to in-hospital and post-hospital interventions. Correlative testing and regression analyses will be performed only as *exploratory* to examine relationships between potential predictors and participant outcomes. In addition, repeated measures analyses will be explored to examine change over time. Our small sample size will limit our ability to perform multivariable testing with all potential confounding variables but will allow for identification of potentially important predictors and sample size justification for future larger studies. Our proposed sample is large enough to demonstrate feasibility of longitudinal follow-up, estimate the prevalence of abnormalities after COVID-19 for the purposes of planning, and identify longitudinal trends in recovery and potentially important predictors for future analyses. All analytic plans will be agreed upon by the FIRE CORAL committee after review of the distribution of abnormalities from the first 40 completed visit.

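### The only feasibility success rule counts a single visit, so it cannot support a conclusion about longitudinal follow-up

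*Protocol article*

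**What the plan says.** The protocol article states what is to be shown in several places:

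- Abstract, Methods and analysis: "The primary objective of the study is to determine the feasibility of longitudinal assessments investigating multiple domains of recovery from COVID-19".
- Introduction, first aim: "examine the feasibility of longitudinal assessments investigating multiple domains of recovery in parallel".
- Sample size: the sample was kept small "to demonstrate the feasibility of conducting longitudinal in-person research in COVID survivors".
- Statistical analysis plan: "Our proposed sample is large enough to demonstrate feasibility of longitudinal follow-up".
- FIRE CORAL study aim, primary objective: "To examine the feasibility of conducting rigorous in-person follow-up testing of participants discharged from the hospital following COVID-19 illness". The word *longitudinal* does not appear in this objective.

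The single decision rule is in Sample size. The study succeeds if "at least 50 participants out of proposed 80 (62.5%, 95% CI 52–73%) complete at least one study visit". What each participant must do to count is therefore only to "complete at least one study visit".

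On visits, Study procedures places the first at 3 to 9 months after discharge and invites everyone back at 12 months. The intermediate visit is optional (Table 1 footnote). The Statistical analysis plan uses the 12-month visit to describe recovery among those who come back. It sets no threshold for that return.

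**The concern.** Four sections say the study is to show that longitudinal assessment or follow-up is feasible. The rule that decides success needs one attendance per person, and one attendance contains no repeat measurement. Followed as written, the rule can report success when nobody returns at 12 months.

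This is not detail left to a fuller document. The article states the rule, its threshold and its confidence interval, and then states a conclusion that the rule does not test. The study is meant to help plan a larger one. Whether people come back for a second in-person visit is a main uncertainty for a longitudinal design, and it has no part in the verdict.

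**Working it through.** **Inputs from the article.** Threshold 50 of 80, with a stated 95% CI of 52–73% (Sample size). Expected completion rate 75%, quoted in the same section from guidance on feasibility studies. 12-month visit offered to all (Study procedures).

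**Assumptions.** The article gives no 12-month retention, so retention r among first-visit completers is varied from 0% to 100%. The 75% is taken as the first-visit rate for illustration; the article does not tie it to a particular visit.

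**Step 1: the plan's own figure.** 50/80 = 0.625. Wald interval: 0.625 ± 1.96 × √(0.625 × 0.375 / 80) = 0.625 ± 0.106, which is 51.9% to 73.1%. This matches the stated 52–73%, so the arithmetic of the rule is sound. The question is what the rule measures.

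**Step 2: the limiting case.** Suppose 50 of 80 attend once and none returns at 12 months. The rule reads 50 ≥ 50 and is met. The observed 12-month return is 0/50 (exact 95% CI 0 to 7.1%), or 0/80 (0 to 4.5%).

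**Step 3: how the rule responds to retention.** Let X be the number of the 80 who meet a criterion, binomial with n = 80.

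- One-visit rule: P(X ≥ 50) with p = 0.75.
- Same count, both visits required: P(X ≥ 50) with p = 0.75 × r.

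| Retention r | 0.75 × r | P(one-visit rule met) | P(at least 50 of 80 with both visits) |
|---|---|---|---|
| 0% | 0 | 0.995 | 0 |
| 50% | 0.375 | 0.995 | 0.000005 |
| 70% | 0.525 | 0.995 | 0.046 |
| 80% | 0.60 | 0.995 | 0.37 |
| 90% | 0.675 | 0.995 | 0.86 |
| 100% | 0.75 | 0.995 | 0.995 |

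The third column does not move, so the rule carries no information about repeat attendance. The last column only shows the contrast and does not propose 50 of 80 as the two-visit threshold.

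**Step 4: participants with two in-person visits.** With exactly 50 first-visit completers, 50% to 80% retention leaves 50 × 0.5 = 25 to 50 × 0.8 = 40 of 80 (31% to 50%). If all 80 attended first and 80% returned, it would be 80 × 0.8 = 64 of 80 (80%). The rule is met in each case.

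**The case against.** **The study aim section does not say longitudinal.** Its primary objective is in-person follow-up testing, and a one-visit rule fits that wording reasonably well. This stands, and it means the objective wordings themselves disagree. It does not rescue the rule, because the Abstract, Introduction, Sample size and Statistical analysis plan all make the longitudinal claim.

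**One visit already adds to a longitudinal record.** Participants have hospital data and specimens from the parent cohort, telephone assessments at 1, 3, 6 and 12 months, and any available pre-illness tests. It would therefore be wrong to call a one-visit result purely cross-sectional, or to say that only 25 to 40 of 80 would have longitudinal data. That count refers to repeat in-person visits and assumes the minimum of 50 first attendances. But the Sample size section speaks of longitudinal research done in person, and telephone contacts do not test that. Completing the 1- or 3-month call is also an entry condition.

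**The primary analysis is descriptive.** The 12-month results would be described, so planners could see the number returning. This stands, and nothing shows that a larger study would be planned on the one-visit figure alone. The success verdict would still be silent on return.

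**Two stronger readings are tempting.** A reader might infer that the rule also neglects the multiple domains. Only the Abstract and Introduction wordings mention domains, a visit is itself a battery across domains, and what counts as completing it may be defined in the full protocol. A reader might also infer that tests "performed as part of routine clinical care within the specified study timeframe will be used in lieu of dedicated study procedures" should not count towards feasibility. The Discussion presents embedding research in existing care as intended, to reduce burden and cost, so excluding those tests would score the design's own method as failure. The documents support neither inference.

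**Conclusion.** The point holds in this form: the one success rule cannot support the stated conclusion that longitudinal follow-up is feasible, and the article words its primary objective in ways that need reconciling. That the rule gives the same verdict from 0% to 100% 12-month retention follows from the text alone. The probabilities (0.995 for the rule throughout, against 0.37 at 80% retention for the same count of two-visit completers) rest on an assumed 75% first-visit rate, assumed retention and binomial independence.

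A reader might go further and require 50 of 80 on a two-visit endpoint. The documents give no basis for carrying that number over. At 80% retention it would probably fail a study whose retention many would think acceptable. The threshold is for the sponsor to justify.

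**What to change.** First, use one wording of the primary objective in the Abstract, Introduction, FIRE CORAL study aim, Sample size and Statistical analysis plan sections. Then do one of the following:

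1. **Narrow the claim.** Keep the one-visit rule, say that it concerns feasibility of in-person follow-up, and remove the Statistical analysis plan's statement that the sample demonstrates feasibility of longitudinal follow-up. This costs only wording.
2. **Add a measure that matches the claim.** Prespecify the proportion of the 80 who complete both the first and the 12-month visit, with its 95% CI, against a threshold with a stated rationale. Base the longitudinal conclusion on that and keep the one-visit count for in-person attendance. The 12-month visit is already offered to everyone, so no new data are needed. The cost is a stricter criterion, and a verdict that waits for the 12-month window, which closes at 15 months.

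Under either option, completion by domain and the share of tests taken from routine care can be tabulated as supporting information. Routine-care tests should stay in the success count.

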#### Statistical analysis plan

To examine the feasibility of long-term follow-up, we will describe the number of participants enrolled and the proportion that returned for in-person follow-up (primary objective). We will perform summary or descriptive statistics to describe the prevalence of abnormalities of pulmonary function, chest CT imaging, and functional status in the enrolled participants (secondary objective). Among participants who return for a 12-month visit, we will describe the trajectory of recovery of pulmonary function and functional status between first and last study visits. Additionally, we will test the relationships (correlative analyses) between outcomes with key independent variables including participant demographics, severity and duration of illness, pre-hospital function, and exposure to in-hospital and post-hospital interventions. Correlative testing and regression analyses will be performed only as *exploratory* to examine relationships between potential predictors and participant outcomes. In addition, repeated measures analyses will be explored to examine change over time. Our small sample size will limit our ability to perform multivariable testing with all potential confounding variables but will allow for identification of potentially important predictors and sample size justification for future larger studies. Our proposed sample is large enough to demonstrate feasibility of longitudinal follow-up, estimate the prevalence of abnormalities after COVID-19 for the purposes of planning, and identify longitudinal trends in recovery and potentially important predictors for future analyses. All analytic plans will be agreed upon by the FIRE CORAL committee after review of the distribution of abnormalities from the first 40 completed visit.

## Data quality, ethics, and dissemination

FIRE CORAL is approved via the PETAL Network central Institutional review board (IRB) at Vanderbilt University and via reliance agreements with the site IRBs. A multi-faceted quality assurance approach will be utilized to ensure data quality and consistency: (1) use of Manuals of Operation for training and reference, (2) regular meetings between local investigators and study coordinators to answer questions and ensure consistency in evaluations across study sites, (3) conferences between all Investigators for the same purposes, (4) ongoing quality assurance review and training updates, (5) data entry into a database with extensive automated checks of data validity, and (6) ongoing review of descriptive statistics by Investigators with detailed review of selected data. The Strengthening of the Reporting of Observational studies in Epidemiology (STROBE) guidelines will be followed for study dissemination [29].

## Discussion

The purpose of the FIRE CORAL study is to comprehensively assess recovery following hospitalization for COVID-19 in a national, multicenter pilot cohort. Data from the study will advance our understanding of the biological, clinical, and patient-related factors associated with long-term impairments following hospitalization for COVID-19 and may inform the development and testing of targeted interventions to mitigate those impairments. Early studies suggest that many patients hospitalized for COVID-19 have persistent symptoms and impairments in respiratory and physical function [6, 30]. Moreover, it is expected that patients requiring an ICU admission for COVID-19 disease may develop impairments associated with post-intensive care syndrome (PICS). Findings from patients surviving ARDS, which is common in individuals hospitalized for COVID-19, demonstrate that long-term impairments lead to reduced quality of life, lost wages with inability to return to work, and increased risk of morbidity, re-hospitalization, and mortality [31–36]. Thus, there is a profound need to understand the recovery of COVID-19 following hospitalization.

FIRE CORAL will expand on the existing literature on COVID recovery in several important and distinct ways. First, FIRE CORAL is unique in that it will enroll participants from geographically and ethnically diverse communities across the USA, increasing the interpretability and generalizability of our findings to the broader pulmonary community. Prior observational cohort studies describing post-COVID impairments following hospitalization were primarily single-center cohort studies from China [37–40] and Europe [41–43]. US cohorts describing post-COVID impairments following hospitalization also remain restricted to regional experiences, and there are no multicenter, national cohorts, to date, describing longitudinal changes in pulmonary function and imaging across the USA [44]. Second, participants in FIRE CORAL will undergo a comprehensive assessment that includes both symptom assessments as well as objective pulmonary and physical functional assessments Most studies to date evaluating patients after COVID-19 hospitalization have used survey methods and focused primarily on patient-reported symptoms [6, 45]. Objective pulmonary measurements, including lung function and CT imaging following COVID-19 hospitalization were reported in some of the observational cohorts earlier in the pandemic from China [37–40] and Europe [41–43]; however, data describing physical recovery following COVID-19 hospitalization remain limited. An additional unique and novel strength of FIRE CORAL will be the availability of biospecimens spanning the recovery trajectory that will help to inform our mechanistic understanding of the development of post-COVID sequela across illness severities. Finally, FIRE CORAL will recruit participants regardless of ongoing symptoms; in fact, some participants will likely have already achieved a “return to baseline health” at their initial post-hospital visit. This may allow us to elucidate a biological pattern of early/sustained recovery in addition to a pattern a persistent inflammation and/or illness.

Methodologically, FIRE CORAL incorporates several innovations with respect to the conduct of longitudinal cohort studies in survivors of serious illness. It leverages existing trial and clinical infrastructure to study longer term outcomes in a more pragmatic, cost-effective manner. Embedding the research infrastructure within existing care models eases the burden of participation for patients, particularly those recovering from severe illness, while also minimizing broader research costs. Additionally, this allows for direct, real-time feedback on care delivery for COVID19 survivors reducing the implementation gap that exists between research and clinical care. Therefore, even as a pilot study, FIRE CORAL has the potential to inform current practices in research on long-term functional outcomes of acute respiratory illness by demonstrating the feasibility of incorporating research activities across the care continuum for hospital survivors and building a network of facilities equipped for trials in the post-hospital setting. Inclusion of a geographically diverse network of US institutions provides a more generalizable understanding of the post-hospital COVID-19 experience and allows for targeted enrollment in centers with larger proportions of underserved and underrepresented communities to better understand disparities in post-COVID recovery. Together, these features will make FIRE CORAL an important contribution to the burgeoning literature on PASC.

## Conclusions

The enclosed FIRE CORAL protocol presents a novel, longitudinal cohort of post-COVID-19 pulmonary and functional recovery after hospital discharge. This in person phenotyping will extend our knowledge of the long-term effects of COVID-19 and provide insight into biologic mechanisms of incomplete pulmonary recovery after COVID-19. This will establish a longer-term biorepository after COVID-19 that will help to inform future studies of COVID-19 recovery.

## Data Availability

Not applicable.

## Abbreviations

ARDS: Acute respiratory distress syndrome
BLUE CORAL: Biology and Longitudinal Epidemiology of PETAL COVID-19 Observational Study
COVID19: Novel coronavirus SARS-Cov2
CT scan: Computerized tomography scan
FIRE: Functional, Imaging, and Respiratory Evaluation
HRQL: Health-related Quality of Life
IRB: Institutional Review Board
LTO: Long-term outcomes
NHLBI: National Heart, Lung and Blood Institute
PASC: Post-Acute Sequela of COVID19
PETAL Network: Prevention and Early Treatment of Acute Lung Injury Network
PFT: Pulmonary function test
